#### Auditory biofeedback

ABF will be supplied by a lumbar-mounted smartphone (mHealth Technologies s.r.l., Bologna, Italy). The ABF system detects AP and mediolateral (ML) linear accelerations near the body’s CoM. The participant wears headphones and the ML inclination with respect to gravity is encoded as a sound in either the right or left ear while the AP tilt is encoded as changes in pitch as the person leans forward or backward. When the body is in perfect equilibrium, the system is quiet. A calibration test is used to determine optimal balance parameters such that the auditory feedback increases only when the person exceeds their baseline sway by 1° or the tilt of the trunk during gait exceeds an established threshold [42, 53]. Both AP and ML feedback will be supplied to the participant during static balance exercises. During dynamic balance exercises, only ML feedback will be provided. During balance exercises, participants will be instructed to utilize the auditory sounds provided by the ABF system to maintain balance and keep the system quiet (i.e., minimal deviations from the stable calibration).

#### Primary and secondary outcome measures

The primary outcome measure is the change between pre-rehabilitation, post-rehabilitation, and 6-week follow-up testing of the model-based parameters of the novel CSMI test (Table 2). Secondary outcome measures are the changes between pre-rehabilitation, post-rehabilitation, and 6-week follow up testing of the clinical and objective balance measures described in Study 1 and in Table 3. Additional secondary outcome measures from the at-home inertial sensors will include activity rate and average turning speed and number of turns.

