### Study 1: Characterization of balance deficits

#### Assessment procedures

All people who are eligible per phone screening will come into the clinic for the informed consent process. An investigator will verbally explain the consent form, allow the person ample time to read through the consent form and then will acknowledge consent by signing the form. All subjects will first read and sign consent forms. For study 1, 65 mTBI participants and 65 control subjects will be assessed on a battery of tests designed to measure vestibular function, sensorimotor integration, static and dynamic balance, cognition, reaction time, clinical sensory loss, and self-reported symptoms. All protocols have been approved by the OHSU Institutional Review Board.

Participants will complete a novel central sensorimotor integration test (CSMI test) [22] on a modified research NeuroCom platform using custom-designed, low-amplitude (2° and 4° peak-to-peak) pseudorandom stimuli that apply continuously repeated cycles of wide bandwidth surface-tilt and/or visual-tilt stimuli with individual tests lasting ~5 min. The participants’ anteroposterior (AP) body displacement at shoulder and hip levels, and surface and visual surround rotation angles will be recorded. Subjects will perform 8 trials (2 amplitudes x 4 test conditions) in one session with trials presented in a randomized order and interspersed with rest breaks (Table 1). Anthropometric measures will be obtained for the purpose of estimating body mechanics needed for later analysis (moment of inertia, mass, height of center of mass, CoM) [22].

**Table 1 Tab1:** Aim 1 CSMI test conditions and sensory weight comparisons

Condition	Vision	Support Surface	Visual Surround	Sensory Weight Comparisons
1	EC	PRS	--	*W* _*prop*_ vs. *W* _*vest*_
2	EO	PRS	Fixed	*W* _*prop*_ vs. *W* _*vis*_ *+ W* _*vest*_
3	EO	Fixed	PRS	*W* _*vis*_ vs. *W* _*prop*_ *+ W* _*vest*_
4	EO	PRS	PRS	*W* _*prop*_ *+ W* _*vis*_ vs. *W* _*vest*_

*EC* eyes closed, *EO* eyes open, *PRS* pseudorandom stimulus

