#### Primary outcome measure

The primary outcome measures of central sensorimotor integration are the parameters derived from a model-based interpretation of CoM sway evoked by pseudorandom stimuli (Table 2). The procedure for calculating these parameters is to (1) calculate CoM angular displacement from experimental measures of hip and shoulder displacement on each test trial, (2) use Fourier methods to calculate a frequency response function, FRF (e.g. Fig. 2d) [46], and (3) adjust parameters of a model of the balance control system represented by the Fig. 2a block diagram using a constrained optimization algorithm (Matlab “fmincon” function; The Mathworks, Inc., Natick, MA) until the model-derived FRF optimally matches the experimental FRF (e.g. model-derived FRFs in Fig. 2d) [22, 47]. This analysis procedure will be applied to each of the 8 individual tests performed by each subject. The full set of model parameters are defined in Table 2.

**Table 2 Tab2:** Balance control model parameters

*W* _*vis*_ *, W* _*prop*_ *, W* _*vest*_	Sensory weights of visual, proprioceptive, and vestibular contributions
*K* _*p*_ *, K* _*d*_	Neural controller parameters (sensory-to-motor transform)
*K* _*t,*_	Gain constant (torque feedback pathway)
*t* _*d*_	Net feedback time delay

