**Fig. 2 Fig2:**
[figure not shown]
CSMI methods with example data and analysis. (**a**) A feedback control model forms the basis for identifying model parameters (Table 2) that account for experimentally evoked body-in-space (BS) sway, representing angular tilt of the body center-of-mass (CoM), evoked by support surface (SS) and/or visual surround (VS) rotations. (**b**) An example of one cycle of a pseudorandom surface-tilt stimulus that evoked the CoM body sway (averaged across 5 stimulus cycles) shown in (**c**) for a Control subject and TBI subject. (**d**) Frequency domain analysis of stimulus/response data in (**b**) and (**c**) yields frequency response functions (FRFs) expressed as gain (ratio of CoM response amplitude to stimulus amplitude) and phase (timing of response relative to stimulus) measures as a function of frequency components in the pseudorandom stimulus. Parameters of the model in (**a**) are calculated by a fit procedure that finds parameters that optimally account for the FRF gain and phase data

The parameters include sensory weights that represent the relative contributions of proprioceptive, visual, and vestibular sensory information to balance control such that in each of the 4 test conditions the sum of weights equals 1. These weights are known to vary with test conditions that alter the availability (e.g. eyes open or closed) or reliability (e.g. varying stimulus amplitudes) of sensory information and are affected by sensory abnormalities (22, 24). For condition 1 tests (surface tilt stimulus with eyes closed) the model fit to the experimental FRF provides a measure of the proprioceptive contribution (Wprop). With eyes closed, the visual contribution (Wvis) is zero and therefore the vestibular contribution is Wvest = 1 – Wprop. Condition 2 tests also use a surface tilt stimulus but eyes are open with both visual and vestibular cues providing accurate orientation information. The model fit again provides an estimate of Wprop but now 1 – Wprop = Wvis + Wvest. Condition 3 tests present a visual tilt stimulus where the model fit provides a measure of Wvis and 1 – Wvis = Wprop + Wvest. Finally condition 4 tests simultaneously present the same surface and visual-tilt stimulus. In this condition the model fit provides a measure of Wprop + Wvis with Wvest = 1 – (Wprop + Wvis).

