#### Statistical analysis

To determine if objective/novel measures of balance will better distinguish people with mTBI from control subjects than clinical measures, we will use logistic regression classification models. Improvements in classification will be determined by calculating the area under the curve (AUC) of the receiver-operator characteristic and then comparing AUC for each traditional clinical measure with the novel objective measures. Significance will be assessed using bootstrapping to determine if the observed differences in AUC are greater than would be expected by chance at a level of 0.05.

To determine if a subset of people with mTBI will have abnormal CSMI test measures, even without peripheral vestibular or ocular motor deficits, we will use descriptive statistics to characterize the distribution of CSMI test measures and vestibular/ocular motor scores. We will define CSMI test measures and vestibular/ocular motor scores as abnormal if the scores are greater than 2 standard deviations from the mean in controls. We will then classify mTBI subjects into one of 4 CSMI-vestibular/ocular motor categories 1) abnormal CSMI –abnormal vestibular/ocular motor scores, 2) abnormal CSMI –normal vestibular/ocular motor scores, 3) normal CSMI –abnormal vestibular/ocular motor scores, 4) normal CSMI –normal vestibular/ocular motor scores.

To determine if the observed relationship between poorer static/dynamic balance performance and mTBI is regulated/mediated by central sensorimotor integration, we will use mediation analysis. Mediation analysis [49] will allow for the partitioning of the association between mTBI and chronic imbalance into two parts, the direct relationship of mTBI on balance impairment as well as the causally mediated effect of mTBI on central sensorimotor integration, which, in turn is having the actual effect on imbalance. These varying generative mechanisms of balance deficits will be assessed by utilizing linear models relating mTBI to CSMI test measures alongside models of mTBI and CSMI test measures jointly affecting imbalance using the apportionment methods described by Baron and Kenny [49].

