#### Statistical analysis

To determine if ABF intervention improves central sensorimotor integration, we will build linear regression models to simultaneously evaluate the change in CSMI measures reflecting central sensorimotor integration and the effect of ABF compared to standard of care. Our outcome will be the change in pre- versus post-rehabilitation program CSMI measures; using the change (difference) in CSMI measures will control for the correlation of the repeated pre- and post- measures within an individual as well as maximizing the number of covariates we can potentially add into the regression models. Covariates of interest are vestibular/ocular motor scores, PTSD, Veteran versus civilian status, age, and gender. In addition, we will determine whether rehabilitation improved the static and dynamic balance metrics that were measured at the pre- and post-rehabilitation testing visits.

To determine if people with CSMI impairment show sustained improvement in static and dynamic balance after rehabilitation, even after ABF is discontinued, we will use linear mixed effects regression modeling which will include a third time point of interest (6 weeks after the rehabilitation intervention has stopped). Time will be treated as a categorical variable in order to evaluate changes in CSMI scores and balance during specific time periods, in this case, between the cessation of the intervention and the 6 weeks post-intervention follow-up. We will explicitly test the significance of a group by time interaction to determine if participants in the ABF rehabilitation group showed sustained improvements in outcomes beyond that experienced by participants with the standard of care. If applicable, we will then stratify the analysis by those with abnormal/normal measures of vestibular/ocular motor function to assess the relationship between vestibular/ocular motor function deficits and sustained improvement in CSMI score and balance.

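### Study 2's primary outcome is the whole CSMI parameter table, about 40 parameters with none singled out, although the sample size rests on only two of them

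*Protocol article*

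**What the plan says.** - **Primary outcome** (protocol article, Study 2, Primary and secondary outcome measures): change between pre-rehabilitation, post-rehabilitation and "6-week follow-up testing of the model-based parameters of the novel CSMI test (Table 2"). The reference is to Table 2 as a whole, which lists three sensory weights, Kp, Kd, Kt and td. Table 3 also marks the CSMI test as primary for both studies.
- **Number of fits** (Study 1, Assessment procedures and Primary outcome measure): "Subjects will perform 8 trials (2 amplitudes x 4 test conditions) in one session", and "This analysis procedure will be applied to each of the 8 individual tests performed by each subject".
- **Constraint on the weights** (text after Fig. 2): "in each of the 4 test conditions the sum of weights equals 1". Each condition therefore yields one estimated weight, or weight sum, and its complement.
- **Analysis** (Study 2, Statistical analysis): linear regression models, with "Our outcome will be the change in pre- versus post-rehabilitation program CSMI measures". A mixed model with a group-by-time test then adds the 6-week visit.
- **Sizing** (Study 2, Sample size): based on Kp in the eyes-open surface-tilt test (t = -2.02) and Wvis in the fixed-surface visual-tilt test (t = 2.07), from 3 mTBI pilot subjects and 12 controls. It gives d = 0.748, alpha 0.10 and 72% power with 10 per group; 20 per group are planned.
- **Abnormality** (Study 1, Statistical analysis): "abnormal if the scores are greater than 2 standard deviations from the mean in controls", with no direction given.
- **Abstract, Methods**: names daily activity as the Study 2 primary outcome. Table 3 lists it as secondary.

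**The concern.** A primary outcome should say which result decides the question. Here it is a table of parameters, repeated over 8 trials, with no parameter, condition or amplitude placed first. The authors did have two parameters in mind, since the sizing uses them, but the outcome section gives them no special status. The stated power therefore belongs to no declared primary test.

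At stake is how a favourable result would be read. If each parameter is tested in its own regression, one or more nominally significant differences between arms is a probable outcome even if auditory biofeedback adds nothing. The abstract sets out to determine efficacy, and the results are meant to help power a later trial. A parameter picked because it came out best would pass on an inflated effect size.

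**Working it through.** **1. The plan's own figure.** With d = 0.748 and n = 10, a paired within-group t-test at two-sided 0.10 (noncentral t, 9 df, noncentrality 0.748 x sqrt(10) = 2.365) has 70.5% power, close to the stated 72%. A between-arm t-test with 10 per arm (18 df, noncentrality 0.748 x sqrt(10/2) = 1.673) has 48.6%. The stated repeated-measures setting reaches about 72% between arms, two-sided, only with an assumed pre-post correlation near 0.74. The point below does not depend on this.

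**2. Count of primary parameters.**
- Trials: 2 amplitudes x 4 conditions = 8.
- Free parameters per trial: 1 weight + Kp + Kd + Kt + td = 5.
- Total: 8 x 5 = 40 for the pre-to-post change alone.

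**3. Chance of at least one false positive, no true effect.** For k independent tests this is 1 - (1 - alpha)^k.
- k = 40, alpha 0.05: 1 - 0.95^40 = 0.871.
- k = 40, alpha 0.10: 1 - 0.90^40 = 0.985.
- k = 2, for comparison: 1 - 0.95^2 = 0.098; 1 - 0.90^2 = 0.190.

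Parameters fitted in the same people will be correlated, and the documents give no correlations. Simulating 40 correlated normal outcomes with 20 per arm gives:

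| Assumed correlation | alpha 0.05 | alpha 0.10 |
|---|---|---|
| 0.6 within a parameter across trials, 0 between parameters | 73% | 92% |
| 0.9 within, 0.2 between | 46% | 70% |
| 0.7 between all 40 | 39% | 61% |
| 0.8 between all 40 | 28% | 47% |

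**4. What naming the primary buys.** With 20 per arm and 0.748 taken as the standardised between-arm difference (38 df, noncentrality 0.748 x sqrt(20/2) = 2.365), power for one parameter is 75.1% at two-sided 0.10 and 63.5% at 0.05. Keeping all 40 under Bonferroni leaves 21.2% (0.10/40) or 15.4% (0.05/40).

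**5. Direction of change.** The pilot t values imply d = 2.02 x sqrt(1/3 + 1/12) = 1.30 for Kp and 2.07 x sqrt(1/3 + 1/12) = 1.34 for Wvis, with opposite signs. To compare signed change with change in absolute distance from the control mean, assume a 0.75 SD move toward normal in one arm, baseline SD 1, pre-post correlation 0.6, 20 per arm and two-sided 0.05. The SD of change is sqrt(2 x 0.4) = 0.894, so the standardised signed effect is 0.75/0.894 = 0.84. Simulated power:

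| Baseline deficit | Share deviating each way | Signed | Distance |
|---|---|---|---|
| 1.3 SD | all one way | 73% | about 41% |
| 1.3 SD | 50/50 | 5% | about 41% |
| 3 SD | all one way | 73-74% | 73% |
| 3 SD | 50/50 | 5% | 73% |

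**The case against.** **It is a pilot, and its conclusions are cautious.** Study 2 is called a randomized pilot, meant to inform a larger trial. The Discussion says only that biofeedback may facilitate rehabilitation. This stands as mitigation: a false positive leads to another trial, not to adoption. It does not remove the point, because the abstract speaks of efficacy and the analysis section tests significance.

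**Error control belongs in an analysis plan.** That stands too, and the absence of a multiplicity rule from this article is not the finding. The identity of the primary outcome is stated here, and it is stated as a whole table.

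**The visit is already chosen.** Largely true. The first regression uses pre-to-post change, and the 6-week visit serves a separate retention hypothesis. The parameter, condition and amplitude remain open.

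**Stronger readings that the documents do not support.**
- A reader might infer that biofeedback will be declared effective on any one of 40 tests. The article states no such rule; the figures above are conditional on one-by-one testing.
- A reader might infer, from the two-sided 2 SD rule and the stress on heterogeneity, that opposite improvements will cancel. The rule permits this but does not show it. No passage reports people deviating both ways on the same parameter, each pilot deficit has one group-level sign, and the heterogeneity described concerns balance deficits, recovery and etiology.
- It is tempting to make distance from the control mean the primary. At the pilot-sized deficit in one direction that would lower power from 73% to about 41%.

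**Conclusion.** The point holds. The Study 2 primary outcome is fixed too broadly: about 40 parameters, when the authors sized the study on two. If the parameters are tested one by one, the chance of at least one false positive is 87% at 0.05 and 98.5% at the plan's 0.10 under independence. It is roughly 39-73% and 61-92% under the strong correlations assumed here, and lower still if all 40 correlate at 0.8. The count of 40 follows from the text; the correlations are assumptions. Cancellation of signed changes is a conditional risk that merits a sensitivity analysis. It is not an established defect.

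**What to change.** - Name as primary the between-arm difference in pre-to-post change in Kp (condition 2) and Wvis (condition 3), at one stated amplitude, with Holm across the two at a stated overall alpha.
- Prespecify the direction that counts as improvement for each, from the pilot deficits. Their t values have opposite signs, so the direction has to be written separately for each parameter.
- Make all other parameters, conditions, amplitudes and the 6-week contrast secondary or exploratory.
- Add change in distance from the control mean as a sensitivity analysis.
- Reconcile the abstract's primary outcome with the outcome section and Table 3.

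**Cost.** No new data are needed, but this changes the primary outcome wording in the protocol and not only in an analysis plan. Other CSMI parameters can no longer carry a primary claim. Holm's first step halves alpha: at an overall 0.10, each parameter is first tested at 0.05, where power is 63.5% under the assumption in step 4, against 75.1% for a single primary.

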#### Sample size

We powered the intervention study to detect improvement in the CSMI test deficit we found in our pilot subjects. Conservatively, 20 subjects will be recruited for both the experimental treatment and standard of care groups to provide results that are capable of powering a more in-depth future clinical trial investigating rehabilitation for balance deficits in mTBI patients. The CSMI test deficits observed in 3 mTBI pilot subjects and 12 healthy controls were used to power the study. Specifically, the CSMI parameter Kp under open eye surface tilting (t = -2.02, *p* = 0.065) and visual sensory weight Wvis under fixed surface visual tilting (t = 2.07, *p* = 0.060) were used to calculate sample size based on independent sample t-tests. Rehabilitation-based differences within the TBI cohort are not expected to be as extensive as those identified between mTBI subjects and controls. However, an effect size at 50% of the magnitude of the difference observed between mTBI and controls in the preliminary data (Coehn’s d = 0.748) would still yield 72% power with α = 0.10 in a repeated measures framework in as little as 10 subjects per group. Conservatively, we will recruit 20 subjects each for the experimental treatment and standard of care groups to provide results that are capable of powering a more in-depth future study investigating rehabilitation for balance deficits in mTBI patients.

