The heterogeneity of balance deficits and varied rates of recovery after mTBI suggest varied etiologies and a need for interventions that address the underlying causes of poor balance function. Over-simplified clinical balance measures often do not account for the complex integration of sensory and motor systems. Therefore, the first goal of this study is to characterize balance deficits in people with mTBI who have chronic, non-resolving balance deficits compared to healthy control subjects without a history of mTBI. We hypothesize that a) objective measures of central sensorimotor integration, static and dynamic balance will better distinguish people with mTBI from control subjects than clinical measures, b) a subset of people with mTBI will have abnormal central sensorimotor integration test measures, even without peripheral vestibular or ocular motor deficits, and c) the relationship between poorer static/dynamic balance performance and mTBI is regulated/mediated by central sensorimotor integration. The second goal is to determine if augmenting a traditional balance rehabilitation program with a wearable-sensor based ABF system improves central sensory integration in patients with chronic mTBI compared to the standard balance rehabilitation program. Our central hypothesis is that chronic balance deficits after mTBI result from impairments in central sensorimotor integration that may be helped by rehabilitation that challenges balance while simultaneously providing feedback on balance performance. We hypothesize that a) central sensorimotor integration scores will improve with rehabilitation and ABF will increase the improvement of central sensorimotor integration scores beyond the standard of care, b) intervention with ABF will improve objective measures of balance and c) people with central sensorimotor integration impairment will show sustained improvement in central sensorimotor integration scores and balance after rehabilitation with ABF.

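### Study 2's power statement does not follow from its own inputs: half the pilot difference is 0.65 to 0.67, not 0.748, and 72% power with 10 per group is unsupported for the ABF-versus-standard comparison

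*Protocol article*

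**What the plan says.** The Study 2 sample size section of the protocol article gives the source of the effect size: "The CSMI test deficits observed in 3 mTBI pilot subjects and 12 healthy controls were used to power the study". Two parameters are named. One is "the CSMI parameter Kp under open eye surface tilting (t = -2.02", with p = 0.065; the other is "visual sensory weight Wvis under fixed surface visual tilting (t = 2.07", with p = 0.060. These "were used to calculate sample size based on independent sample t-tests".

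The section expects rehabilitation effects to be smaller than the mTBI-control gap. It therefore takes "an effect size at 50% of the magnitude of the difference observed between mTBI and controls in the preliminary data (Coehn’s d = 0.748", and says that this "would still yield 72% power with α = 0.10 in a repeated measures framework in as little as 10 subjects per group". It then calls the planned size conservative: "we will recruit 20 subjects each for the experimental treatment and standard of care groups".

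The Background hypothesises that scores will improve with rehabilitation and that "ABF will increase the improvement of central sensorimotor integration scores beyond the standard of care". The Study 2 statistical analysis section models pre-post change and the effect of ABF against standard care, and adds a group-by-time test over three visits. Sidedness, the SD behind d and a pre-post correlation are not given.

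**The concern.** The section prints group sizes, t values, an effect size, alpha, a sample size and a power, so the chain can be checked. Two links fail. The effect size is not half of what the t values imply, and the power is not what an independent-samples test gives for two groups of 10. The section also leaves open whether the 72% refers to improvement within a group or to the difference between arms.

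At stake is how the trial's sensitivity is described. Twenty per arm is presented as a comfortable margin over 10. If 10 per arm does not have 72% power for the arm difference, that margin is smaller than it looks, and so is the support it offers for planning the later trial.

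**Working it through.** **Inputs, all from the Study 2 sample size section.** Pilot groups of 3 and 12; |t| = 2.02 and 2.07; d = 0.748, described as 50% of the observed difference; alpha 0.10; 10 per group; planned 20 per group. Power is computed from the noncentral t distribution.

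**1. Effect size.** For a pooled two-sample t-test, d = t × √(1/n₁ + 1/n₂), with √(1/3 + 1/12) = 0.6455.

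- Check on the t values: at 13 degrees of freedom, t = 2.02 gives p = 0.064 and t = 2.07 gives p = 0.059. These agree closely with the printed 0.065 and 0.060, so the pooled test fits.
- Kp: 2.02 × 0.6455 = 1.304; half is 0.652.
- Wvis: 2.07 × 0.6455 = 1.336; half is 0.668.
- For 0.748 to be half, the full d would be 1.496, which needs t = 1.496 / 0.6455 = 2.32 and p = 0.037. Neither parameter shows this.
- If 0.748 is instead the full difference, half is 0.374.

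**2. The stated 72%, with d = 0.748 and 10 per group.**

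| Test | Noncentrality | Power at alpha 0.10 |
|---|---|---|
| Two groups, two-sided | 0.748 × √(10/2) = 1.673, 18 df | 48.6% |
| Two groups, one-sided | 1.673, 18 df | 63.8% |
| One group of 10, pre-post, two-sided | 0.748 × √10 = 2.365, 9 df | 70.5% |

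The one-group test comes closest, if 0.748 is read as the standardised mean change. At d = 0.374, two-sided power is 20.8% (two groups) or 29.4% (one group).

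**3. Effect of a pre-post correlation ρ.** If d is in cross-sectional SD units with equal variances, the SD of change is σ√(2(1 − ρ)). The effect on change is then d / √(2(1 − ρ)). For two groups of 10 at d = 0.748 and two-sided alpha 0.10:

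| ρ | 0.3 | 0.5 | 0.6 | 0.7 | 0.74 | 0.8 |
|---|---|---|---|---|---|---|
| Power | 38.9% | 48.6% | 56.2% | 66.7% | 72.1% | 81.5% |

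So 72% needs ρ of about 0.74 two-sided, or 0.62 one-sided. With the derived effect of 0.652 to 0.668, it needs about 0.79 to 0.80 two-sided.

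**4. The planned 20 per arm, arm difference in SDs of the change score (38 df, two-sided).**

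| Effect | alpha 0.10 | alpha 0.05 |
|---|---|---|
| 0.652 | 64.8% | 52% |
| 0.668 | 66.6% | 54% |
| 0.748 | 75.1% | 64% |
| Effect for 80% power | 0.80 SD | 0.91 SD |

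If 0.652 is in cross-sectional SD units, 20 per arm at two-sided alpha 0.10 gives about 65%, 73% and 83% at ρ = 0.5, 0.6 and 0.7.

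**The case against.** The strongest defence is that the section invokes a repeated-measures framework and the analysis uses change scores. A high enough pre-post correlation brings two arms of 10 to 72%. Values of 0.74 or 0.62 are not implausible on their face, the documents exclude neither, and the full protocol behind the article may state one. This stands as far as it goes: 72% cannot be called impossible for the arm comparison. But the pilot contrast that the section describes is cross-sectional and supplies no such correlation. Nor does the defence explain 0.748. An unequal-variance t-test could bring the full Wvis difference to about 0.745 if the mTBI SD were about 0.29 of the control SD, but no such SDs are stated. Half of that would in any case be about 0.37.

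A reader might infer from the 70.5% that a one-group pre-post calculation was used by mistake. The document does not show this. The match is near but not exact, it needs its own unstated assumption, and the text speaks of subjects per group and independent-samples tests.

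A reader might also infer that the power was computed for a comparison the trial does not need. That is not supported either. The Background lists improvement with rehabilitation as part of the same hypothesis, and the sample size section says the study is powered to detect improvement.

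On the use of an mTBI-control gap as the reference, the section acknowledges that rehabilitation effects will be smaller and halves the gap. Whether half is discount enough for a difference between two active programmes is a matter of judgement.

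Finally, the plan recruits 20 per arm in a study called a pilot, and the Discussion draws no conclusion from a null ABF result. This limits the consequence.

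**Conclusion.** The point holds in a limited form. The printed effect size is inconsistent with the printed t values: half the pilot difference is 0.65 to 0.67 on the pooled test, which reproduces the printed p values closely. The 72% with 10 per group is unsupported, not disproved, for ABF versus standard care. On the printed inputs it is 49% two-sided or 64% one-sided, and reaching 72% depends on an unstated correlation.

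For the planned 20 per arm, power at the derived effect is about 65% to 67% at two-sided alpha 0.10, in SDs of the change score and without a covariate gain. Dropout and multiplicity over several CSMI parameters are not counted. A pre-post correlation above 0.5 would raise the figure if the effect is in cross-sectional units. This should be fixed, but it does not threaten the design: Study 2 is a pilot and its size can stand.

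**What to change.** Change the Study 2 sample size section only, and keep 20 per arm.

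- Correct the halved effect size to 0.65 to 0.67, or show the data and formula that give 0.748.
- Say whether the power refers to improvement within a group or to the difference between arms.
- Replace the sentence on 72% and 10 per group with the between-arm power for 20 per arm. State the sidedness, which SD the effect is expressed in, and the assumed pre-post correlation with a range.

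Possible wording: *With 20 per arm, the comparison of ABF with standard care on pre-post change has about 65% to 67% power at two-sided alpha 0.10 (52% to 54% at 0.05) for an arm difference of 0.65 to 0.67 SD of the change score. It has 80% power for 0.80 SD (0.91 SD at 0.05). If 0.65 is expressed in cross-sectional SDs, power at two-sided alpha 0.10 is about 65%, 73% and 83% for assumed pre-post correlations of 0.5, 0.6 and 0.7.*

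The cost is wording only, with no added participants or procedures. The downside is that the stated power becomes less favourable.
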